### Interventions

#### Bowel preparation

According to the standard bowel preparation regimen recommended by the Chinese Bowel Preparation Guidelines (37), enrolled subjects orally administered a single 3 L dose of polyethylene glycol electrolyte solution (Jiangxi Hengkang Pharmaceutical Co., Ltd., Lot No. H20020031) as a one-time intake on the examination day, along with initiation of a low-residue diet 24 h prior to colonoscopy. All patients must consume PEG solution 4 to 6 h prior to the endoscopy, drinking 250 mL every 10 min and completing it within a 2-h timeframe. To ensure protocol adherence, two groups received standardized verbal bowel preparation instructions from researchers during colonoscopy scheduling, complemented by detailed written materials outlining preparation steps to minimize comprehension and compliance. Patients in different study groups were allocated to spatially isolated designated wards during TEAS treatment, with strict restrictions on cross-ward activities.

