### Randomization and blinding

This single-blinded trial implemented CONSORT-compliant randomization and blinding protocols (36), and subjects were assigned to the TEAS group and the sham-TEAS group in a 1:1 ratio. To ensure assessment objectivity, screening and outcome assessors remained blinded to treatment allocation status throughout the study period. All recordings were deidentified by removing all patient identifiers and temporal markers to eliminate assessment bias. The TEAS-administering acupuncturists maintained awareness of treatment allocation while remaining blinded to study outcomes. A computer-generated block randomization system with concealed allocation utilized numbered, sealed envelopes containing group assignments, secured by ward nurses until post-allocation unblinding. Primary endpoints were evaluated by two gastroenterologists independently conducted blinded assessments by reviewing endoscopic videos. A standardized operational protocol (fixed electrode stimulation duration) was implemented for double-blind control, while enabling dynamic adjustment of stimulation intensity based on individual tolerance thresholds. A blinding assessment will be conducted after colonoscopy completion and before unblinding, using a standardized questionnaire asking patients: “Which treatment do you think you received? (A. Active TEAS; B. Sham TEAS; C. Uncertain).” The success of blinding will be quantified by calculating the Bang Blinding Index.

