#### TEAS and sham-TEAS

TEAS Protocol: The TEAS intervention protocol employed an acupoint combination targeting *Neiguan* (PC6) and *Zusanli* (ST36) (see Figure 2 for anatomical landmarks). PC6 acupoint is located on the anterior forearm, 2 cun proximal to the transverse wrist crease, between the tendons of the palmaris longus and flexor carpi radialis muscles. ST36 acupoint is situated on the anterolateral aspect of the leg, 3 cun inferior to the lower border of the patella, one finger-breadth lateral to the anterior crest of the tibia. Pre-intervention anatomical validation by acupuncturists (<3 mm positioning tolerance). The stimulation system comprised hydrogel self-adhesive electrodes (diameter: 20 mm) interfaced with a transcutaneous acupoint electrical stimulator (SNM-FDCM01, Ningbo Maida Medical Instrument Company, Ningbo, China). The intervention period overlapped with the PEG administration period and lasted 1 h from the first dose of PEG ingestion (Figure 3). The stimulation parameters were set as follows: a train on-time of 2 s and off-time of 3 s, pulse width of 0.5 ms, pulse frequency of 25 Hz, and amplitude of 2–10 mA (at the maximum level tolerated by the subject).

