### Outcomes

#### Primary outcome

The primary outcome measure was the rate of adequate bowel preparation, which was assessed by two gastroenterologists through independent review of endoscopic videos using the Boston Bowel Preparation Scale (BBPS) (33). The BBPS was applied to each of the three segments of the colon (right, including cecum and ascending colon; transverse, including hepatic and splenic flexures; and left, including descending colon, sigmoid and rectum). Each colon region received a “segment score” ranging from 0 to 3, and these scores were summed to calculate a total BBPS score (0–9) (refer to Appendix). Adequate bowel preparation was defined as a total BBPS score ≥6 with each colon segment scoring ≥2 after standard washing and air insufflation for luminal distension during colonoscopy (13, 44). Endoscopists maintained blinding to group allocation throughout the trial. All endoscopic imaging was independently evaluated by two gastroenterologists, with final diagnoses established through consensus deliberation and unresolved discrepancies resolved by a third-party senior specialist.

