#### Secondary outcomes

Defecation parameters

Following TEAS/sham-TEAS interventions, patients documented their defecation parameters in the record sheets, including first defecation time, total defecation frequency, and final stool consistency.

Colonoscope outcomes

The evaluated parameters encompassed four key indicators: insertion time, withdrawal time, cecal intubation rate (CIR), and adenoma detection rate (ADR). The insertion phase was defined as commencing with initial rectal visualization and concluding when the endoscope tip traversed the ileocecal valve into the cecal caput. Withdrawal time represents the duration from cecum to anal canal during meticulous mucosal inspection in screening or diagnostic procedures without therapeutic interventions, with a minimum 6-min benchmark indicating thorough pathological evaluation. CIR, which reflects procedural completeness through comprehensive cecal visualization including anatomical landmarks, must be maintained at ≥95% to ensure examination adequacy. ADR calculated as the percentage of colonoscopies with at least one adenoma identified.

Adverse reaction

Research staff documented all adverse reactions occurring during the bowel preparation process and post-colonoscopy, including nausea, vomiting, abdominal pain, distension, headache, and dizziness (refer to Appendix). The incidence rate of adverse reactions was calculated as (number of cases with adverse reactions)/(total number of cases).

Satisfaction and follow-up colonoscopy

At the conclusion of the treatment period, all participants were surveyed regarding their satisfaction with bowel preparation and their willingness to have a follow-up colonoscopy. The details are presented in Appendix.

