### Adverse reaction

Adverse reaction associated with bowel preparation and colonoscopy procedures—including nausea, vomiting, abdominal pain, bloating, headache, and dizziness—were prospectively categorized by blinded independent assessors.

1) Transient symptoms requiring no intervention, with preserved procedure tolerability;
2) Symptom-driven procedural pauses (<5 min) without compromising examination completion;
3) Intolerable symptoms necessitating premature procedure termination;

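### As written, study arm determines the treatment ward, so a ward difference in care cannot be told apart from a TEAS effect, and ward can reveal the arm to staff handling adverse reactions

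*Protocol article*

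**What the plan says.** All references are to the protocol article.

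- **Ward follows arm.** Interventions, Bowel preparation: "Patients in different study groups were allocated to spatially isolated designated wards during TEAS treatment, with strict restrictions on cross-ward activities". No ward is described as holding both arms, and no change of wards between arms is described.
- **When the separation applies.** TEAS and sham-TEAS: "The intervention period overlapped with the PEG administration period and lasted 1 h from the first dose of PEG ingestion".
- **Who is said to be blinded.** Randomization and blinding: "screening and outcome assessors remained blinded to treatment allocation status throughout the study period". Primary outcome: "Endoscopists maintained blinding to group allocation throughout the trial". Appendix, Adverse reaction: these reactions "were prospectively categorized by blinded independent assessors". Only the acupuncturists are named as knowing the allocation.
- **When adverse reactions are collected.** Secondary outcomes: "Research staff documented all adverse reactions occurring during the bowel preparation process and post-colonoscopy".
- **Protection of the primary reading.** Randomization and blinding: "All recordings were deidentified by removing all patient identifiers and temporal markers to eliminate assessment bias".
- **Primary analysis.** Statistical analysis specifies a logistic model adjusted for baseline covariates. Ward is not mentioned.

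**The concern.** Individual randomisation balances patients between arms. It does not balance what happens to them afterwards if arm also decides where they are looked after. Here the place of care differs by arm during the very hour in which stimulation is given and much of the PEG is drunk. If preparation goes somewhat better in one ward than the other for reasons unrelated to electrode position, that difference appears in the primary result with nothing to mark it as a ward effect. It could create an apparent benefit or hide a real one.

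The second issue is blinding. Staff who record or grade adverse reactions during bowel preparation may see which ward a patient is in. If ward goes with arm, one disclosure of the mapping reveals the allocation of every patient there.

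**Working it through.** **1. The plan's own figure.** Inputs from Sample size: 70% versus 85%, two-sided alpha 0.05, power 90%, 20% dropout. With pooled variance under the null, the mean rate is 0.775:

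n = [1.96·√(2·0.775·0.225) + 1.2816·√(0.70·0.30 + 0.85·0.15)]² / 0.15² = (1.157 + 0.745)² / 0.0225 ≈ 160.8, so 161 per group.

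161 / 0.80 = 201.25, so 202 per group and 404 in total. The stated sizes reproduce; no figure in the plan is disputed.

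**2. How much of the preparation falls in the separated hour.** Bowel preparation gives 3 L at 250 mL every 10 min. That is 12 portions over 120 min, so 6 portions, or 1.5 L, fall within the first 60 min at the stated pace. About half of the intake takes place in the arm's own ward.

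**3. Why adjustment fails.** Write logit P(adequate) = a + b·arm + c·ward. If ward equals arm, only b + c can be estimated. With several wards per arm, the ward indicators within an arm add up to the arm indicator, so the problem is the same. Baseline covariates do not help, because ward care comes after randomisation.

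**4. What an undetected ward difference would do.** The ward difference d is an assumption; the document gives none. Take a sham rate of 70%, no TEAS effect, m analysed per arm, and a two-sided pooled z test:

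P(p<0.05) = Φ[(d − 1.96·se₀)/se₁] + Φ[(−d − 1.96·se₀)/se₁]

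Here se₀ = √(2·p̄·(1−p̄)/m), se₁ = √([p₁(1−p₁) + p₂(1−p₂)]/m), p₁ = 0.70, p₂ = 0.70 + d, and p̄ is their mean.

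Example, d = 0.05 and m = 202: se₀ = √(0.39875/202) = 0.0444 and se₁ = √(0.3975/202) = 0.0444. The first term is Φ(−0.836) = 0.202 and the second is 0.001, giving 0.203.

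| Assumed ward difference | 161 per arm | 202 per arm |
|---|---|---|
| 0 points | 5.0% | 5.0% |
| 2 points | 6.8% | 7.3% |
| 3 points | 9.2% | 10.2% |
| 5 points | 17.1% | 20.3% |

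The rate rises with the number of patients, so a larger trial does not cure the problem.

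**5. The opposite direction.** Suppose TEAS truly gives 85% but its ward costs 5 points, taking the two effects as additive. The comparison is then 80% versus 70%. The same formula gives a 54.5% chance of significance at 161 per arm and 64.2% at 202, against 90.0% and 95.3% without the ward difference.

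**6. Blinding, with the passages side by side.** Adverse reactions are documented during bowel preparation, which includes the hour in the arm-specific ward, and the Appendix calls those who grade them blinded. The article describes no step that keeps ward from them. For the primary outcome it does describe a step: identifiers and time markers are removed from the recordings.

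**The case against.** **The text does not fix one permanent ward per arm.** It speaks of wards in the plural and says nothing about nursing teams. A condensed article may leave rotation to the full protocol. This stands as a limit: the point rests on the plain reading. If rotation exists, stating it and recording ward would largely answer the confounding concern.

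**Care is standardised.** Both arms have the same PEG regimen and diet, the same verbal and written instructions, and sham procedures that mirror the active ones, and operators are trained and audited. This makes a large ward effect less plausible. It does not remove the nesting: the verbal instructions are given at scheduling, and nothing stated covers care inside the wards.

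**Separation protects patient blinding.** Keeping the arms apart plausibly stops patients comparing electrode sites, although the article does not give this reason. It is a good reason to keep the separation, and it does not require that each ward always hosts the same arm.

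**Stronger readings that a reader might infer, and that the document does not support:**
- *All outcomes lose their blinding.* The BBPS readers work from de-identified videos. Satisfaction is rated by patients, who get the same device and settings at sham points. Being among patients of the same arm does not tell them which arm it is.
- *Endoscopists are unblinded.* That would require them to learn both the ward and the arm it hosts, and the article does not say that they do.
- *Custody of the envelopes shows that ward reveals arm.* That the envelopes were "secured by ward nurses until post-allocation unblinding" is a separate matter of allocation concealment.
- *The wards differ in coaching, mobility, toilet access or onward transfer.* The article reports no such differences, and transfer falls outside the stated hour.

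**Conclusion.** The concern holds on the plain reading of the text. Ward is nested in arm during the first hour of PEG intake, so the primary comparison estimates the TEAS effect plus any ward effect, and the planned analysis cannot divide the two. The size and direction of any ward effect are unknown. The figures of about 10% and 20% for assumed differences of 3 and 5 points are illustrations at 202 per arm with a 70% sham rate and no TEAS effect; they are not evidence that the wards differ. It would also go too far to say that randomisation has failed: patient characteristics remain balanced by design, and what is not separated is care after allocation.

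On blinding, the conclusion is confined to staff who record or grade adverse reactions during preparation. It is a risk created by the layout, and that these staff know the mapping is an inference. Adverse reactions are analysed as exploratory, which limits the consequence for the main conclusions.

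**What to change.** **For patients still to be treated**
- Keep the arms physically apart, but alternate which ward hosts which arm on a fixed schedule (for example weekly). An alternative is screened bays for both arms in the same wards under one nursing team.
- Record ward for every patient and include it as a covariate in the primary logistic model. Once each ward has hosted both arms, b and c in the model above can be estimated separately.
- Withhold ward, and the alternation schedule, from endoscopists and from those who grade adverse reactions. Leave ward off the endoscopy request and the grading form.

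**For patients already treated in fixed wards** (enrolment was planned from May 2025 to June 2026)
- Tabulate ward by arm, and state that TEAS and ward effects cannot be separated in these patients.

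**If wards already rotate,** say so in the protocol, and record and adjust for ward as above.

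**Cost.** A short amendment and modest ward logistics; the target stays at 161 evaluable and 202 randomised per arm. If bays are shared, there is slightly more chance that patients compare electrode sites. Screens and the existing exclusion of people familiar with acupoints limit this, and alternating separate wards avoids it.

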#### Colonoscopy

All colonoscopies were conducted with the CF-H290l high-resolution adult video colonoscope (Olympus, Tokyo, Japan) by senior endoscopists (≥5 years experience). The endoscopists were blinded to the study’s hypotheses, objectives and patient randomization. Sedation for the colonoscopy was administered using a combination of alfentanil and propofol.

#### TEAS and sham-TEAS

TEAS Protocol: The TEAS intervention protocol employed an acupoint combination targeting *Neiguan* (PC6) and *Zusanli* (ST36) (see Figure 2 for anatomical landmarks). PC6 acupoint is located on the anterior forearm, 2 cun proximal to the transverse wrist crease, between the tendons of the palmaris longus and flexor carpi radialis muscles. ST36 acupoint is situated on the anterolateral aspect of the leg, 3 cun inferior to the lower border of the patella, one finger-breadth lateral to the anterior crest of the tibia. Pre-intervention anatomical validation by acupuncturists (<3 mm positioning tolerance). The stimulation system comprised hydrogel self-adhesive electrodes (diameter: 20 mm) interfaced with a transcutaneous acupoint electrical stimulator (SNM-FDCM01, Ningbo Maida Medical Instrument Company, Ningbo, China). The intervention period overlapped with the PEG administration period and lasted 1 h from the first dose of PEG ingestion (Figure 3). The stimulation parameters were set as follows: a train on-time of 2 s and off-time of 3 s, pulse width of 0.5 ms, pulse frequency of 25 Hz, and amplitude of 2–10 mA (at the maximum level tolerated by the subject).

**Figure 2 fig2:**
[figure not shown]
Location of acupoints and sham-acupoints. Graphical elements by Servier Medical Art (https://smart.servier.com), licensed under CC BY 4.0 (https://creativecommons.org/licenses/by/4.0/).

**Figure 3 fig3:**
[figure not shown]
The administration of TEAS treatment protocol.

Sham-TEAS Protocol: Sham acupoint stimulation was performed using the same devices to provide identical parameters as TEAS, with sham points positioned outside the anatomical course of relevant meridians: the sham-point of PC6 is approximately 15 cm up to the elbow joint and lateral to the real PC6 acupoint and the sham-point of ST36 is approximately 10 cm down to the knee and lateral to the real ST36 acupoint. The temporal schedule and ancillary procedures (electrode placement duration, PEG coordination) mirrored the intervention group.

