### Statistical analysis

All statistical analyses were performed using SPSS 29.0 and GraphPad Prism 10.4, adhering to the intention-to-treat (ITT) principle. Continuous variables were tested for normality using the Shapiro–Wilk test; normally distributed data were expressed as mean ± standard deviation, and non-normally distributed data as median [interquartile range]. Categorical variables were presented as frequencies and percentages. For the primary outcome (rate of adequate bowel preparation), a multivariable logistic regression model was employed to adjust for baseline covariates. Missing data were handled using Multiple Imputation by Chained Equations (MICE); 20 imputed datasets were generated, and the imputation model included all baseline variables, the grouping variable, and the primary outcome measure. To control the type I error rate for multiple secondary outcomes, a hierarchical strategy was adopted. The primary outcome was tested at *α* = 0.05. Among secondary outcomes, colonoscopy indicators were designated as key secondary endpoints and were corrected using the Holm-Bonferroni method. For these endpoints, insertion and withdrawal times (continuous variables) were compared using independent *t*-tests or Mann–Whitney *U* tests as appropriate, and cecal intubation and adenoma detection rates (categorical variables) were compared using Chi-square or Fisher’s exact tests. The remaining secondary outcomes, including bowel movement parameters, patient satisfaction scores, and adverse reactions, were treated as exploratory analyses; no multiplicity correction was applied, and *p*-values are presented for descriptive reference only. Safety profiles were described by comparing the incidence and severity of adverse events (Chi-square test) and patient satisfaction (Wilcoxon rank-sum test). Protocol deviations were addressed by per-protocol sensitivity analyses to verify the robustness of the results. A two-sided *p* < 0.05 was considered statistically significant.

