### Safety assessment

All enrolled patients were included in the safety assessment. Safety outcomes encompassed predefined adverse events (including ear skin rash, dizziness, palpitation, and intolerable diarrhea requiring intervention) during treatment and follow-up phases. All safety-related data were meticulously documented for safety findings.

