Acupuncture is a nonpharmaceutical technique that originated in China and has been used for over 3,000 years. TEAS is a modification of traditional acupuncture (58–60), which combines the advantages of acupuncture and percutaneous electrical nerve stimulation. Unlike traditional acupuncture requiring skin penetration, this transcutaneous approach exhibits notable application prospects via its non-invasive nature, user-friendly operation, and portability (27, 61–63), while concurrently reducing infection risks and improving patient compliance (64). In recent years, a growing number of investigations have put a spotlight on the therapeutic effects of TEAS in intestinal dysmotility disorders. Clinical trials demonstrated that ST36 acupoint stimulation effectively enhances spontaneous bowel movements, alleviates constipation symptoms, and improves quality of life (65), while PC6 application demonstrates marked efficacy in reducing postoperative nausea and vomiting incidence within 24 h (66). While transabdominal or abdominal surface stimulation is theoretically more direct, limb acupoint TEAS is a superior adjunctive choice based on current evidence and operational feasibility. This study implemented a standardized stimulation parameter protocol (0.5-ms pulse width, 25 Hz frequency, and 2–10 mA amplitude) (42, 43, 67), developed based on prior clinical trial evidence to ensure intervention stability and experimental reproducibility. This study recruited only inpatients, which may limit the generalizability of our findings to the broader outpatient colonoscopy population. The inpatient setting was chosen to ensure protocol adherence and intervention fidelity, but future multicenter, pragmatic trials in outpatient settings are needed to validate the real-world applicability of TEAS as an adjunct to bowel preparation. Additionally, although we standardized endoscopist experience and withdrawal time, ADR remains influenced by multiple operator-dependent factors, and residual confounding cannot be fully excluded.

This protocol employs validated stimulation parameters (25 Hz frequency, 60-min sessions) combined with standardized laxative regimens, aiming to establish TEAS as a safe strategy for enhacing bowel preparation and alleviating adverse effects (e.g., bloating and nausea).

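### Both arms are electrically stimulated, so the between-arm adverse-event test says nothing about harm they share, and a null result cannot support calling TEAS safe

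*Protocol article*

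**What the plan says.** Under TEAS and sham-TEAS, the active arm is stimulated for 1 h from the first PEG intake at 25 Hz and 0.5 ms pulse width, with an "amplitude of 2–10 mA (at the maximum level tolerated by the subject"). The sham paragraph then states: "Sham acupoint stimulation was performed using the same devices to provide identical parameters as TEAS". It adds: "The temporal schedule and ancillary procedures (electrode placement duration, PEG coordination) mirrored the intervention group". The sham electrodes sit away from PC6 and ST36. There is no third arm.

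On safety, Statistical analysis says: "Safety profiles were described by comparing the incidence and severity of adverse events (Chi-square test"). The same section treats adverse reactions as exploratory: "no multiplicity correction was applied, and *p*-values are presented for descriptive reference only". Secondary outcomes defines the measure: "The incidence rate of adverse reactions was calculated as (number of cases with adverse reactions)/(total number of cases"). Safety assessment covers all enrolled patients and predefines events, "including ear skin rash, dizziness, palpitation, and intolerable diarrhea requiring intervention".

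The closing sentence of the Discussion describes the protocol as "aiming to establish TEAS as a safe strategy" that improves preparation and eases symptoms such as bloating and nausea.

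**The concern.** A randomised comparison shows only what differs between the arms. Here that is electrode position. Harm that comes from passing current through the skin, or from the electrodes, arises in both arms and largely cancels in the comparison.

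The article names a between-arm test as the way safety is described and, separately, states an aim of establishing safety. It nowhere notes that the control patients have the same exposure. A frequent stimulation-related event could then appear as balanced between arms, and the balance could be taken as reassurance. At stake is the trial's safety conclusion, not its efficacy result.

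**Working it through.** **Plan's own figure.** For 70% versus 85%, two-sided 0.05 and 90% power, with the pooled-variance formula:

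n = [1.960·√(2·0.775·0.225) + 1.282·√(0.70·0.30 + 0.85·0.15)]² / 0.15² = (1.157 + 0.745)² / 0.0225 ≈ 160.8, so 161 per arm.

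161/0.80 = 201.25, so 202 per arm and 404 in total. The stated size reproduces. It concerns the primary outcome and supplies only the denominators used below.

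**What differs between the arms.**

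| Feature | TEAS | Sham |
|---|---|---|
| Stimulator | SNM-FDCM01 | same |
| Pulse settings | 25 Hz, 0.5 ms, 2 s on / 3 s off | same |
| Amplitude | 2–10 mA, to tolerance | same rule |
| Duration and timing | 1 h from first PEG intake | same |
| Electrode sites | PC6, ST36 | points away from both |

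**Harm shared fully.** If an event has risk r in both arms, the true difference is r − r = 0. The chi-square test then rejects at about its nominal level, 5%, whatever r is and however many patients are enrolled. This follows from the definition of the test and is not an estimate about this trial.

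**Harm shared in part.** Background rate, excess and shared fraction are assumptions. Let b be the background rate, h the excess from stimulation and f the fraction of h that the sham also carries, so that p₁ = b + h and p₂ = b + f·h. With 202 per arm and two-sided 0.05:

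power = Φ[(p₁ − p₂ − 1.96·SE₀)/SE₁], where SE₀ uses the pooled rate and SE₁ the separate rates.

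Example with b = 10%, h = 10 points, f = 0.5: p₁ = 0.20, p₂ = 0.15, SE₀ = √(0.175·0.825·2/202) = 0.0378, SE₁ = √[(0.16 + 0.1275)/202] = 0.0377. Power = Φ[(0.05 − 0.0741)/0.0377] = Φ(−0.64) = 26%.

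| Fraction f carried by sham | b = 10%, h = 10 points | b = 37%, h = 10 points |
|---|---|---|
| 0 (no-current control) | 81% | 53% |
| 0.25 | 53% | 33% |
| 0.50 | 26% | 17% |
| 0.75 | 9% | 7% |
| 1 | about 5% (nominal level) | about 5% (nominal level) |

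The 37% background is the gastrointestinal intolerance rate with PEG that the Discussion cites, used here only as an illustration.

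**What absolute rates can show.** With no events, the exact two-sided 95% upper limit is 1 − 0.025^(1/n).

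- 0/202: 1 − 0.025^(1/202) = 1.8%.
- 0/404: 1 − 0.025^(1/404) = 0.9%.
- Hypothetical 10/202: 5.0% (2.4% to 8.9%).
- Hypothetical 20/404: 5.0% (3.0% to 7.5%).

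These limits describe the risk in stimulated patients directly, whatever happens in the other arm.

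**The case against.** The case on the other side is substantial, and much of it stands.

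- **Purpose of the comparison.** The hypothesis includes relief of preparation symptoms, and most listed adverse reactions are symptoms of that kind. For that aim a comparison with stimulated sham points is appropriate. This stands, and the test should stay.
- **Status of the test.** Its p-values are descriptive, and no passage says that a non-significant result will count as proof of safety. A reader might infer such a decision rule, but the documents do not contain one. The difficulty is narrower: the named comparison cannot bear the stated aim, and nothing warns against reading it that way.
- **Absolute rates are already planned.** Incidence is defined as cases over total, categorical data are given as frequencies and percentages, and severity is graded in the Appendix. A frequent event would therefore be visible in the TEAS column. This stands too. What is left is to let those rates, with their limits, carry the safety conclusion. Interval method and table layout could be left to an analysis plan; the mismatch between test and aim is in the article itself.
- **Device harm in general.** A reader might infer that the comparison can show no device harm at all. That goes too far. The rationale section gives PC6 and ST36 site-specific effects on motility, so harm by that route, for example the predefined intolerable diarrhea, can differ by arm and be seen.
- **Identical current.** A reader might also infer that both arms receive the same current. The settings and the titration rule are the same, but amplitude follows individual tolerance, so the delivered current may differ between patients and between arms.
- **Lack of an unstimulated arm.** This is a design choice, stated openly, and a perceptible sham serves patient blinding, which the trial assesses. It is not an error.

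**Conclusion.** The point holds for harm that both arms share. For such events the between-arm test is uninformative when the risk is equal. It is weak when most of the excess is shared: power of 7% to 9% at a three-quarters share in the two illustrations, against 53% to 81% with a no-current control. A null difference therefore cannot support the safety aim in the Discussion. The power figures rest on assumed background rates and an assumed 10-point excess; the equal-risk result rests on no assumed rate.

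The point does not extend to acupoint-specific harm or to symptom relief, for which the comparison remains valid.

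Absolute rates have limits of their own. They include background events from PEG, sedation and the procedure, so for dizziness or palpitation they do not attribute the event to the device. Pooling assumes that the event depends on the current or electrodes rather than on their site. The limits of 1.8% and 0.9% assume that all 202 and 404 patients are stimulated and assessed. Sample size and primary analysis are untouched.

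**What to change.** In Statistical analysis:

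1. List the events that could come from the current or electrodes. Palpitation and dizziness are already predefined; electrode-site skin reaction and stimulation pain are examples to consider.
2. For these, make the main safety result the absolute incidence with an exact 95% confidence interval, in each arm and pooled over all stimulated patients.
3. Keep the between-arm comparison as a test of acupoint position and of symptom relief.
4. State that a non-significant difference is not evidence that stimulation is safe, because both arms are stimulated.

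In the Discussion, limit the safety wording to what the absolute rates and their upper limits support.

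The cost is a few sentences, one extra table and a more modest safety claim. No further patients and no unstimulated arm are needed, and no new data provided that these events are being recorded as the Safety assessment section intends.
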